## **8. Adverse events**

### **8.1 Definition of adverse events**

#### **(1) AEs**

An AE is any unfavorable and unintended sign (including laboratory test abnormalities), symptom, or disease occurring to a subject treated with the IP, which does not necessarily have to have a causal relationship to the relevant IP.

#### **(2) ADRs**

An ADR is any unfavorable and unintended event occurring at any dose of the IP for which causal relationship to the IP cannot be ruled out.

#### **(3) Unexpected ADRs (UADRs)**

A UADR is any ADR that differs from available drug information in the profile or the extent of risk of the event in light of the investigator's brochure or the package insert.

#### **(4) SAEs/SADRs**

An SAE/SADR is any AE/ADR occurring at any dose of the IP that meets any of the followings.

- ① resulting in death or life-threatening
- ② requiring hospitalization or prolonged hospitalization
- ③ leading to persistent or significant incapacity or incapacity
- ④ leading to congenital anomaly or birth defect
- ⑤ other important medical event except for the above ① to ④, such as development of blood dyscrasias or drug dependence/abuse.

In this study, hospitalization for any of the following reasons will not constitute an SAE:

- Hospitalization that was planned prior to study
- Hospitalization for medical checkup or recuperation or for cosmetic reasons
- Emergency room visit for no longer than 24 hours. However, an emergency room visit for no longer than 24 hours can be considered an SAE at the discretion of the investigator.

For an event that is not one of the situations listed above but may have a significant medical impact on the health and well-being of the patient, a decision will be made as to the status of seriousness based on the medical judgment of the attending physician and relevant specialists,

and appropriate actions will be taken accordingly.

## 8.2 Collection and documentation of adverse events

- During the study, AEs will be collected from after the 1st dose (Visit 2) to Day 28 after the 2nd dose of the IP (Visit 9). All medical events occurring before the 1st dose of the IP will be documented as medical history.
- SAEs and AESIs will be collected from after the 1st dose (Visit 2) of the IP to the end of follow-up (Visit 11).
- Once AEs grade  $\geq 3$  are occurred during the course of 1st dose (Visit 2) to the end of follow-up (Visit 11), subjects should inform study institution or investigator through telephone call with reference to severity assessment of adverse events in subject diary, and investigator should primarily check symptoms via telephone call. Subjects who requires treatment of AEs by investigator will perform unscheduled visit for treatment with medication.
- Subjects who have the symptoms of COVID-19 infection such as fever or respiratory symptoms should inform investigator about their symptoms as followed by COVID-19 guidelines of Central Disease Control Headquarters·Central Disaster Management Headquarters, and will be instructed to visit study institution to be treated, observed and assessed. Investigator or study coordinator should follow up the AEs in subjects who are not available to visit study institution via telephone call.
- An AE report should include the following information: term of AE, duration (date of onset and date of resolution), severity, causal relationship to the IP, action taken for the IP, outcome, corrective treatment for the AE, and status of immediate AE/SAE.
- The investigator should document AEs as comprehensive diagnostic terms or symptoms using standard medical terminology rather than recording individual symptoms or signs.
- AEs occurring during the study should be followed up until the event is resolved or stabilized or the subject is lost to follow-up. Follow-up of AEs of which date of resolution is unknown as of Day 28 after the 2nd dose (Visit 6) will be determined at the discretion of the investigator.
- AEs occurring after the end of follow-up (Visit 11) will spontaneously be reported by subjects; if a subject reports to the investigator an AE that is considered to be an SADR, the investigator will report to the sponsor.

## 8.3 Assessment of adverse events

### 8.3.1 Severity assessment

Severity of solicited or unsolicited AEs in subjects enrolled in this study will be classified as follows based on the assessment of severity of local and systemic AEs in healthy adults and adolescents in 「MFDS, Guidelines for the assessment of severity of adverse events in vaccine trials」.

#### 8.3.1.1 Solicited local adverse events

| Grade
Item                | Mild
(GRADE 1)                           | Moderate
(GRADE 2)                                                                           | Severe
(GRADE 3)                                                   | Potentially life-
threatening
(GRADE 4) |
|------------------------------|---------------------------------------------|-------------------------------------------------------------------------------------------------|-----------------------------------------------------------------------|-----------------------------------------------|
| Pain                  | No interference with activities             | Repeated use of non-opioid analgesics for > 24 hours or some interference with daily activities | Use of opioid analgesics or severe interference with daily activities | Emergency room visit or hospitalization       |
| Tenderness            | Mild discomfort to touch                    | Discomfort to exercise                                                                          | Considerable discomfort at rest                                       | Emergency room visit or hospitalization       |
| Erythema/redness *    | 2.5~5cm                                     | 5.1~<10cm                                                                                       | ≥10cm                                                                 | Necrosis or exfoliative dermatitis            |
| Induration/swelling * | 2.5~5cm and no interference with activities | 5.1~<10cm or some interference with activities                                                  | ≥10cm or severe interference with daily activities                    | Necrosis                                      |
| Itchiness             | Slight itchiness at the injection site      | Considerable itchiness at the injected limb                                                     | Itchiness at the injected limb and other areas of the body            | Itchiness all over the body                   |

\* Measured local reactions will be graded on the basis of the single longest diameter.

#### 8.3.1.2 Solicited systemic adverse events

| Grade
Item  | Mild
(GRADE 1) | Moderate
(GRADE 2) | Severe
(GRADE 3) | Potentially life-
threatening
(GRADE 4) |
|----------------|-------------------|-----------------------|---------------------|-----------------------------------------------|
| Fever * | 38.0~38.4°C       | 38.5~38.9°C           | 39.0~40.0°C         | >40.0°C                                       |

| Gra
de
Item   | Mild
(GRADE 1)                                                                       | Moderate
(GRADE 2)                                                                                                            | Severe
(GRADE 3)                                                                                          | Potentially life-
threatening
(GRADE 4)         |
|------------------------------|-------------------------------------------------------------------------------------------------|------------------------------------------------------------------------------------------------------------------------------------------|----------------------------------------------------------------------------------------------------------------------|----------------------------------------------------------------|
| Fatigue/malaise
※※ | Easily tolerable and no interference with activities                                            | Some interference with daily activities, making it difficult to perform several activities                                               | Considerable; severe interference with daily activities resulting in loss of abilities to perform several activities | Emergency room visit or hospitalization                        |
| Chills/rigors         | Easily tolerable and no interference with activities                                            | Some interference with daily activities, making it difficult to perform several activities                                               | Severe interference with daily activities resulting in loss of abilities to perform several activities               | Emergency room visit or hospitalization                        |
| Headache              | Easily tolerable and no interference with activities                                            | - Repeated use of non-opioid analgesics for > 24 hours
-Interference with brain function
- Some interference with daily activities | Use of opioid analgesics or severe interference with daily activities                                                | Persistence leading to emergency room visit or hospitalization |
| Myalgia               | Easily tolerable and no interference with activities                                            | Interference with muscle function or some interference with daily activities                                                             | Severe interference with daily activities resulting in loss of abilities to perform several activities               | Emergency room visit or hospitalization                        |
| Joint pain            | Mild pain that does not interfere with function (with inflammation, redness, or joint swelling) | Moderate pain interfering with function but no interference with daily activities (with inflammation, redness, or joint swelling)        | Severe pain interfering with daily activities (with inflammation, redness, or joint swelling)                        | Emergency room visit or hospitalization                        |
| Diarrhea              | 2 to 3 loose stools or < 400 g during a 24-hour period                                          | 4~5 loose stools or 400~800 g during a 24-hour period                                                                                    | ≥6 loose stools or ≥800 g during a 24-hour period or requiring fluid therapy on an outpatient setting                | Emergency room visit or hospitalization                        |
| Vomiting              | No interference with activities or 1~2 times/24                                                 | Some interference with activities or >2 times/24                                                                                         | Severe interference with daily activities or                                                                         | Emergency room visit or hospitalization for                    |

| Gra
de
Item         | Mild
(GRADE 1)                                                                  | Moderate
(GRADE 2)                                                                                        | Severe
(GRADE 3)                                                                                             | Potentially life-
threatening
(GRADE 4) |
|------------------------------------|--------------------------------------------------------------------------------------------|----------------------------------------------------------------------------------------------------------------------|-------------------------------------------------------------------------------------------------------------------------|--------------------------------------------------------|
|                                    | hours                                                                                      | hours                                                                                                                | requiring fluid therapy on an outpatient setting                                                                        | hypotensive shock                                      |
| Abdominal pain              | Weak                                                                                       | Moderate (no treatment required)                                                                                     | Moderate (treatment required)                                                                                           | Severe (hospitalization)                               |
| Mucocutaneous reaction/rash | Erythema (itchiness) or limited macular rash                                               | Extensive, maculopapular rash, dry desquamation                                                                      | Vesication or wet desquamation or ulceration                                                                            | -                                                      |
| Cough                       | Temporary (no treatment required)                                                          | Persistent cough (treatment required)                                                                                | Paroxysmal cough (not controlled by treatment)                                                                          | -                                                      |
| Acute bronchospasm          | - Temporary (no treatment required)
-70-80% of FEV 1 at peak expiratory flow | - Treatment required; recovery to normal with bronchodilator
- 50-69% of FEV 1 at peak expiratory flow | -No recovery to normal with bronchodilator
- 25-49% of FEV 1 at peak expiratory flow; or chest depression | -                                                      |
| Respiratory distress        | Respiratory distress during exercise                                                       | Respiratory distress during normal activities                                                                        | Respiratory distress at rest                                                                                            | -                                                      |

※ Fever is defined as an increase in body temperature to  $\geq 38^{\circ}\text{C}$  based on at least one measurement of the core temperature. Once fever is detected, body temperature should be measured at least twice a day (morning and evening) or at clinically appropriate time points until 2 consecutive measurements of  $< 38^{\circ}\text{C}$  are obtained.

※※ Interference of individual activities refers to deterioration of the individual's function to perform his/her daily activities at work or school or his/her social or personal activities.

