## 5.5 Criteria for study suspension

During the study period, subjects will be monitored for the following ADRs that serve as criteria for study suspension. In the event of ADRs that are the criteria for study suspension, additional enrollment and treatment will be stopped at this time, and the DSMB will meet to decide study continuation.

- 1) Part A study: Grade  $\geq 3$  ADRs occurring within 7 days after the 1st dose in the first 5 subjects
- 2) Part A and Part B studies:
  - ① Grade  $\geq 3$  ADRs occurring within 3 days (Day 0 ~ Day 2) from the respective dosing day and lasting for  $> 1$  day despite active intervention for resolution in  $\geq 15\%$  of all

subjects planned to be enrolled to each study group (Part A:  $\geq 8/50$  subjects, Part B:  $\geq 35/230$  subjects)

- ② SADRs or Grade  $\geq 4$  ADRs occurring within 28 days after the respective dose of the IP

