## 7.2 Endpoints

### 7.2.1 Safety endpoints

- AEs
  - ① Immediate AEs occurring within 30 minutes after each IP dosing
  - ② Solicited local and systemic AEs occurring for 7 days (Day 0~ Day 6) after each IP dosing
    - ✓ Local AEs : pain, tenderness, erythema/redness, induration/swelling, itchiness
    - ✓ Systemic AEs : fever, fatigue/malaise, chills/rigors, headache, myalgia, joint pain, diarrhea, vomiting, abdominal pain, mucocutaneous reaction/rash, cough, acute bronchospasm, respiratory distress
  - ③ Unsolicited AEs occurring within 28 days after the last IP dosing
  - ④ SAEs occurring within 52 weeks after the last IP dosing
  - ⑤ AESIs occurring within 52 weeks after the last IP dosing
- Clinical laboratory tests (hematology/blood chemistry, urinalysis)
- Vital signs
- Physical examination

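### As written, solicited joint pain without inflammation, redness or joint swelling fits none of Grades 1 to 3, so when severe but managed at home it does not count as Grade 3 for the protocol's safety rules

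*Protocol*

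**What the plan says.** Section 7.2.1 lists the solicited systemic events for Day 0 to Day 6 after each dose by name only: "fever, fatigue/malaise, chills/rigors, headache, myalgia, joint pain, diarrhea, vomiting, abdominal pain", and so on. No joint sign is mentioned there.

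The joint-pain row of 8.3.1.2 reads:

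- Grade 1: "Mild pain that does not interfere with function (with inflammation, redness, or joint swelling")
- Grade 2: "Moderate pain interfering with function but no interference with daily activities (with inflammation, redness, or joint swelling")
- Grade 3: "Severe pain interfering with daily activities (with inflammation, redness, or joint swelling")
- Grade 4: "emergency room visit or hospitalization"

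The table has footnotes for fever and for fatigue/malaise, but none for joint pain. Section 8.3.1.3 has a general scale based on daily activities, but it is headed for unsolicited events. No rule says what to do with a solicited event that fits no cell.

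The grades feed live rules. Section 5.5 suspends Part A for Grade 3 or higher "ADRs occurring within 7 days after the 1 st dose in the first 5 subjects". It also has a 15% rule on Grade 3 or higher reactions and a third rule on serious reactions or those of Grade 4 or higher. Section 3.1.1 opens enrolment of the remaining 20 high-dose subjects if no such Grade 3 or higher reaction occurs in the sentinels. Section 8.2 has subjects telephone the site for any event of Grade 3 or higher, using the severity scale in the diary. Section 7.3.4.1 tabulates events by severity.

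**The concern.** The symptom that is solicited and the symptom that is graded are not the same. A subject reports joint pain in a home diary, but the scale below Grade 4 describes joint pain accompanied by visible signs. A subject who cannot carry out daily activities because of joint pain, with no swelling or redness, matches no cell unless an emergency room visit or hospitalization follows.

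The signs are also hard to establish at the time. The first scheduled contact after a dose is a telephone call on Day 2 to 5, and the first scheduled post-dose physical examination is on Day 7, with a window of 3 further days. Subjects receive a ruler and a thermometer, but the protocol describes no method for judging joint inflammation. Sites may therefore leave the event ungraded, ignore the parenthesis, or assign a grade by judgement, and the choice may differ between sites.

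At stake are the consistency of the severity data that serve the Part A primary objective (safety and tolerability) and whether a severe reaction counts in rules that act during the trial.

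**Working it through.** This is a check of wording. The only related figures are the suspension thresholds.

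**1. Thresholds.** Section 5.5 sets 15% of planned subjects. Part A: 0.15 × 50 = 7.5, rounded up to 8. Part B: 0.15 × 230 = 34.5, rounded up to 35. Both match the stated 8/50 and 35/230. They are not in question.

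**2. The row, cell by cell, for joint pain without signs.**

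| Grade | Signs in the cell? | Fits sign-free pain as written? |
|---|---|---|
| 1 | yes | no |
| 2 | yes | no |
| 3 | yes | no |
| 4 | no | yes, if an emergency room visit or hospitalization occurs |

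This is 0 of 3 cells for Grades 1 to 3, and 1 of 4 overall.

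**3. Neighbouring items.** Myalgia Grade 3 is "Severe interference with daily activities resulting in loss of abilities to perform several activities", with no sign. Headache and injection-site pain are graded on interference or analgesic use, also without a sign. Disabling muscle pain is Grade 3; equally disabling joint pain without swelling is not.

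**4. Consequences for severe, related, sign-free joint pain on Day 0 to 6, managed at home and not serious.**

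| Rule | Depends on | Counts as written? |
|---|---|---|
| High-dose sentinel gate, 3.1.1 | Grade 3 or higher | no |
| Sentinel suspension criterion, 5.5 | Grade 3 or higher | no |
| 15% criterion, 5.5 | Grade 3 or higher, plus timing and duration | no |
| Serious or Grade 4 criterion, 5.5 | seriousness or Grade 4 | no, as neither applies |
| Telephone rule, 8.2 | Grade 3 or higher | no |
| Low-dose sentinel review, 7.3.8 | all events over 7 days | yes |
| End-of-Part-A DSMB review, 7.3.8 | all events | yes |
| Incidence tables, 7.3.4.1 | occurrence | yes |
| Severity tables, 7.3.4.1 | grade | undefined |

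**5. Where it bites most.** Each sentinel group has 3 vaccinated subjects and 2 on placebo. One reaction of Grade 3 or higher triggers the rule, so the grade of a single event can decide it. For the low dose, 7.3.8 provides a review that does not depend on grade. For the high dose, 3.1.1 states the gate in terms of grade. Section 3.3.1 describes the same gate more loosely, as safety being confirmed, so the effect rests on the 3.1.1 wording.

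**The case against.** The best defence is that the parenthesis is a descriptor. It is identical in all three cells, so it does not separate one grade from another; severity is carried by the words for pain and interference. It may also come from the national guideline on which the table is said to be based, or from translation. Visits 4 and 7 include an examination of limbs and the musculoskeletal system, so signs can sometimes be checked. All of this is fair, and the intent may well be benign. But the protocol nowhere calls the signs optional, and a reader who applies the cells as printed gets the result above. The guideline is not available here and cannot settle the point.

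Several stronger readings are tempting but are not supported:

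- *Sign-free joint pain has no grade and can never reach the triggers.* Grade 4 needs no sign and satisfies the Grade 3-or-higher condition if the event is related. A serious reaction triggers suspension whatever its grade.
- *A sentinel's reaction would escape review.* Not for the low dose, where 7.3.8 provides for assessment of all solicited and unsolicited events before enrolment continues. The DSMB also reviews the events of all Part A subjects before Part B.
- *The event is lost from the data.* It still counts in frequency and incidence; only its severity category is unclear. Joint pain reported as unsolicited falls under 8.3.1.3, which needs no sign.
- *Some 12 to 46 subjects are affected.* Assuming that 5% to 20% of the 15 + 15 + 100 + 100 = 230 vaccinated subjects report joint pain gives 11.5 to 46. That counts all joint pain at an assumed rate. The subset that is severe, related, sign-free and managed at home is smaller by an unknown amount.

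**Conclusion.** The point holds in a limited form: the joint-pain row conflicts with the solicited item it is meant to grade. The effect is confined to one of 18 solicited items, to the solicited window, and to events without signs and without an emergency room visit or hospitalization. Within those limits it reaches the high-dose sentinel gate, the Grade 3-or-higher suspension criteria, the telephone rule and the severity tables.

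No effect on the chance of a trigger can be calculated. The 15% criterion also requires onset within Day 0 to 2 and duration beyond 1 day despite intervention, and no effect on it is shown. The conclusion assumes that the cells are applied as printed.

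The point is still worth correcting in the protocol. Grades are assigned when events are collected and feed rules that act during the trial, so a later analysis document cannot repair them.

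**What to change.** Reconcile the joint-pain row of 8.3.1.2 with the solicited symptom in 7.2.1, so that the signs are not a condition for Grades 1 to 3. Inserting 'or without' after 'with' in the three parentheses does this. Carry the same wording into the severity scale in the subject diary, and record joint inflammation, redness or swelling as a separate yes/no item. Leave the suspension thresholds in 5.5 as they are.

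The cost is one table line and a diary change. Somewhat more joint-pain events will receive a grade. The wording may also depart from the cited guideline scale; the sponsor should check that source and, if it does depart, say so in the protocol.

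### A related Grade 3 bronchospasm, respiratory distress or rash with a short emergency visit pauses the study only by discretion, while related myalgia with the same visit pauses it automatically

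*Protocol*

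**What the plan says.** Section 5.5 of the protocol sets three suspension criteria. Meeting one stops further enrolment and dosing until the DSMB decides whether the study continues.

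- Criterion 1 (Part A only): a Grade 3 or higher adverse drug reaction (ADR) within 7 days of the first dose in the first 5 subjects. Section 3.1.1 applies this to each dose group.
- Criterion 2-① (Parts A and B): Grade 3 or higher "ADRs occurring within 3 days (Day 0 ~ Day 2) from the respective dosing day and lasting for" more than one day despite active treatment, in at least 15% of planned subjects (8 of 50 in Part A, 35 of 230 in Part B).
- Criterion 2-② (Parts A and B): a serious ADR, or an ADR of Grade 4 or higher, "occurring within 28 days after the respective dose of the IP". One case is enough.

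The grades come from section 8.3.1. In 8.3.1.2, Grade 4 for myalgia, joint pain and diarrhea is an "emergency room visit or hospitalization"; fatigue and chills, and pain and tenderness in 8.3.1.1, have the same entry. For four items the Grade 4 cell holds only a dash: rash, cough, acute bronchospasm and respiratory distress. Grade 3 for three of these is "Vesication or wet desquamation or ulceration" (rash), "No recovery to normal with bronchodilator" among other descriptors (bronchospasm) and "Respiratory distress at rest" (respiratory distress).

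Section 8.1 (4) takes emergency visits of up to 24 hours out of the serious category, but lets the investigator class such a visit as serious.

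**The concern.** For a related event that is not judged serious, the Grade 4 cell alone decides whether criterion 2-② applies. Where that cell is empty, the single-case rule cannot be reached through severity. The resulting order is clinically odd. Muscle pain or diarrhea that leads to a few hours in an emergency room stops a first-in-human vaccine study automatically. Breathlessness at rest with the same visit does so only if somebody decides that it should.

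What is at stake is the automatic pause and the DSMB review that comes with it. This matters most in Part B. Section 7.3.8 schedules DSMB reviews around the Part A sentinels and at the end of Part A. In Part B it provides for a meeting only when a suspension criterion is met or, if needed, for an adverse event of special interest (AESI). Bronchospasm, respiratory distress and rash as such are not on the AESI list.

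**Working it through.** The check applies each rule to one case: a related event, graded on the solicited scale, with an emergency visit of 24 hours or less, and not judged serious.

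**The plan's own figures.** 15% of 50 is 0.15 × 50 = 7.5, rounded up to 8. 15% of 230 is 0.15 × 230 = 34.5, rounded up to 35. Both thresholds in 5.5 reproduce.

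**Criterion 2-② by solicited item.**

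| Item | Grade 4 entry (8.3.1.1, 8.3.1.2) | Does the short visit meet 2-②? |
|---|---|---|
| Pain, tenderness, fatigue, chills, myalgia, joint pain, diarrhea | emergency visit or hospital stay | Yes |
| Headache | "Persistence leading to emergency room visit or hospitalization" | Yes, if persistent |
| Vomiting | emergency visit or hospital stay, with hypotensive shock named | Depends on whether the shock condition applies to the visit as well as the stay |
| Abdominal pain | hospital stay | No, but a Grade 4 exists |
| Rash, cough, acute bronchospasm, respiratory distress | dash | No, and no Grade 4 exists |

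Fever, erythema, induration and itch have Grade 4 entries that do not depend on a visit, so they do not bear on the comparison.

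**Criterion 1.** It covers 5 sentinels in each of 2 dose groups, so 2 × 5 = 10 subjects, after the first dose only. Planned enrolment is 50 + 230 = 280, which leaves 280 − 10 = 270 subjects outside it, together with the sentinels' second doses.

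**Criterion 2-①.** One case is 1 of the 8 subjects needed in Part A, or 1 of the 35 needed in Part B. It counts only events on Day 0-2, so onset on Day 3-6 of the solicited window never counts.

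**Override to Grade 4.** The footnote that makes an event Grade 4 stands under the unsolicited table in 8.3.1.3. It requires a judgement that the event is serious or life-threatening, so it does not reach this case.

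**Limits in time.** Solicited events are collected on Day 0-6 (7.2.1). Immediate events in the first 30 minutes, and unsolicited events, are graded under 8.3.1.3, which does have a Grade 4. The missing grade therefore concerns Day 0-6 after the first 30 minutes, and not the full 28 days of 2-②.

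**Result.** No suspension criterion is met by the single bronchospasm, respiratory distress or rash case. Criterion 2-② is met by the same visit for the seven items in the first row.

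**The case against.** The strongest reply is that the gap closes where it matters. Section 8.1 (4) counts life-threatening, hospitalised and other medically important events as serious, asks for medical judgement on anything with significant impact, and lets the investigator class a short visit as serious. Bronchospasm that resists treatment in a healthy volunteer is the kind of case those clauses address. Once it is called serious and related, 2-② applies.

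There are other routes too:

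- The principal investigator reviews every ADR, and the sponsor decides on continuation when information of significant impact emerges (7.3.7).
- Either of them can stop the study (9.11.1, 9.11.2).
- Section 5.3 can bar the affected subject from the second dose.
- The AESI list includes acute respiratory distress syndrome and erythema multiforme, so some severe respiratory and skin cases already have a DSMB route.
- The grades follow a national guideline for vaccine trials.

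Most of this stands, and it makes the gap narrow. It does not remove the inconsistency. For these items every route to a pause needs somebody's decision, while for myalgia or diarrhea the rule acts by itself.

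A reader might infer that a severe airway reaction could not stop this study, or would go unseen. The protocol does not support that: the discretionary routes exist, and under 8.2 subjects report Grade 3 or higher events by telephone and the investigator checks them. Nor does it show that the grading table is wrong. The fault lies in how 5.5 uses a grade that some items lack.

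**Conclusion.** The point holds as a minor, narrow inconsistency in the single-case suspension rule. Outside the sentinel first doses, one related Grade 3 bronchospasm, respiratory distress or rash on Day 0-6, after the first 30 minutes and with an emergency visit of 24 hours or less, pauses the study only through discretion. Seven other solicited items with the same visit pause it automatically. Cough shares the missing grade.

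The size cannot be put as expected harm, because the protocol gives no event rate. It would be tempting to count the items, days or doses outside the rule and read the share as a risk. Such counts describe only how far the rule reaches.

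The conclusion rests on three assumptions. The dash in four consecutive rows means that no Grade 4 is defined and is not a loss in reading the table. The event is judged related and not serious. The DSMB charter, to which 7.3.8 refers for detail and which is not at hand, adds no trigger of its own; if it does, the gap is smaller still.

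**What to change.** Leave the guideline-based grades as they are and add to criterion 2-② in section 5.5: *or a related Grade 3 solicited acute bronchospasm, respiratory distress or mucocutaneous reaction/rash with onset on Day 0-6 after a dose and leading to an emergency room visit*. Limiting onset to Day 0-6 keeps the clause to the period in which the scale has no Grade 4. Cough can stay out, since an automatic halt for one case of cough is debatable.

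The cost is one clause in a protocol amendment, with IRB approval and, if necessary, approval by the Ministry of Food and Drug Safety. The grading tables, the subject diary and the assessments do not change. The downside is an occasional extra pause for DSMB review, made somewhat more likely because section 8.3.2 treats an event as related unless it meets the not-related definition.
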